# Open-label randomized controlled trial of ultra-low tidal ventilation without extracorporeal circulation in patients with COVID-19 pneumonia and moderate to severe ARDS: study protocol for the VT4COVID trial

**DOI:** 10.1186/s13063-021-05665-z

**Published:** 2021-10-11

**Keywords:** COVID-19, SARS-CoV-2, Acute respiratory distress syndrome, Mechanical ventilation, Ultraprotective ventilation, Ultra-low tidal volume ventilation, Tidal volume

## Abstract

**Background:**

Acute respiratory distress syndrome (ARDS) is a severe complication of COVID-19 pneumonia, with a mortality rate amounting to 34–50% in moderate and severe ARDS, and is associated with prolonged duration of invasive mechanical ventilation. Such as in non-COVID ARDS, harmful mechanical ventilation settings might be associated with worse outcomes. Reducing the tidal volume down to 4 mL kg^−1^ of predicted body weight (PBW) to provide ultra-low tidal volume ventilation (ULTV) is an appealing technique to minimize ventilator-inducted lung injury. Furthermore, in the context of a worldwide pandemic, it does not require any additional material and consumables and may be applied in low- to middle-income countries. We hypothesized that ULTV without extracorporeal circulation is a credible option to reduce COVID-19-related ARDS mortality and duration of mechanical ventilation.

**Methods:**

The VT4COVID study is a randomized, multi-centric prospective open-labeled, controlled superiority trial. Adult patients admitted in the intensive care unit with COVID-19-related mild to severe ARDS defined by a PaO_2_/FiO_2_ ratio ≤ 150 mmHg under invasive mechanical ventilation for less than 48 h, and consent to participate to the study will be eligible. Patients will be randomized into two balanced parallels groups, at a 1:1 ratio. The control group will be ventilated with protective ventilation settings (tidal volume 6 mL kg^−1^ PBW), and the intervention group will be ventilated with ULTV (tidal volume 4 mL kg^−1^ PBW). The primary outcome is a composite score based on 90-day all-cause mortality as a prioritized criterion and the number of ventilator-free days at day 60 after inclusion. The randomization list will be stratified by site of recruitment and generated using random blocks of sizes 4 and 6. Data will be analyzed using intention-to-treat principles.

**Discussion:**

The purpose of this manuscript is to provide primary publication of study protocol to prevent selective reporting of outcomes, data-driven analysis, and to increase transparency. Enrollment of patients in the study is ongoing.

**Trial registration:**

ClinicalTrials.govNCT04349618. Registered on April 16, 2020

**Supplementary Information:**

The online version contains supplementary material available at 10.1186/s13063-021-05665-z.

## Administrative information

Note: the numbers in curly brackets in this protocol refer to SPIRIT checklist item numbers. The order of the items has been modified to group similar items (see http://www.equator-network.org/reporting-guidelines/spirit-2013-statement-defining-standard-protocol-items-for-clinical-trials/).

**Table Taba:** 

Title {1}	Open label randomized controlled trial of ultra-low tidal ventilation without extracorporeal circulation in patients with COVID-19 pneumonia and moderate to severe ARDS. Study protocol for the VT4COVID trial.
Trial registration {2a and 2b}.	ClinicalTrials.gov, NCT04349618
Protocol version {3}	April 12th, 2020 -version 3 January 22th, 2021- version 4
Funding {4}	French Ministry of Health (PHRCI 2020) and Hospices Civils de Lyon

Role of sponsor {5c}	The study funder had no part in study design; collection, management, analysis, and interpretation of data; writing of the report; and in the decision to submit the report for publication. The study funder had no ultimate authority over any of these activities The study sponsor had no part in study design, collection, analysis, and interpretation of data; writing of the report; and in the decision to submit the report for publication, but was involved in data management. The study sponsor had no ultimate authority over any of these activities

## Introduction

### Background and rationale {6a}

Acute respiratory distress syndrome (ARDS) is the most severe complication related to COVID-19 pneumonia and was observed in 78% of the patients under mechanical ventilation in one of the largest prospective case series of COVID-19 patients who required intensive care admission [1]. Current management of COVID-19-related ARDS is based on mechanical ventilation in intensive care units until recovery of lung injury and dexamethasone [2]. However, COVID-19-related 90-day mortality is extremely high, amounting to 34% and 50% in moderate and severe ARDS, respectively [1]. Harmful mechanical ventilation settings might partly explain the mortality of COVID-19 pneumonia. Indeed, 30% of ARDS patients under protective ventilation exhibit tidal hyperinflation on computed tomography, associated with an increase in pro-inflammatory mediators in broncho-alveolar lavage (BAL) [3], suggesting excessive tidal volume (VT). The magnitude of tidal hyperinflation may be even greater in COVID-19 ARDS patients, as we recently observed in a CT study on 13 COVID-19 ARDS patients as compared to 9 non-COVID-19 ARDS patients [4]. Moreover, in a recent observational study on 482 ARDS patients, an increase of 1 mL kg^−1^ predicted body weight (PBW) in initial VT was associated with a 23% increase in adjusted mortality risk, suggesting that small variations in VT at the initial phase of ARDS may impact prognostic [5]. Reducing VT from 6 to 3–4 mL kg^−1^ PBW (so-called ultraprotective ventilation) combined with extracorporeal CO_2_ removal (ECCOR) was associated with a decrease in pro-inflammatory mediators in BAL [6] and a lower mortality in the more severe patients [7].

We have recently performed a pilot multicenter before-after trial [8], on 34 ARDS patients, aiming to provide ultra-low tidal volume ventilation (ULTV) without ECCOR, while aiming to keep arterial pH above 7.20. In this study, VT could be reduced to 4 mL kg^−1^ PBW in 65% and to 5 mL kg^−1^ PBW in 88% of the patients, although 9% of the patients had a pH below 7.20 at inclusion. This strategy was applied during the whole course of ARDS, sedation dose was not significantly increased, and the rate of acute cor pulmonale (6%) was lower than expected. Regarding safety, day 90 mortality amounted to 41% despite the inclusion of some moribund patients, and 32% of the patients developed transient severe acidosis with pH < 7.15.

ULTV without extracorporeal circulation is an appealing technique to protect the ARDS lung in the context of a worldwide pandemic, as it does not require any material and consumables, and may be applied in low- to middle-income countries. We hypothesized that ULTV without extracorporeal circulation is a credible option to reduce COVID-19 mortality and duration of mechanical ventilation, in patients with severe and moderately severe ARDS [2].

### Objectives {7}

The main objective is to assess the benefit of ULTV in comparison with protective ventilation on a composite primary endpoint that will include the all-cause mortality at day 90 as the prioritized criterion and the number of days free from invasive mechanical ventilation (VFD) at day 60 as the second criterion.

The following are the secondary objectives:
To test whether ULTV is associated with a decrease in ARDS all-cause mortality at day 90 after inclusionTo test whether ULTV is associated with higher VFD at day 60 after inclusionTo test whether ULTV is associated with a decrease in time to successful extubationTo test whether ULTV is associated with a shorter hospital stayTo test whether ULTV impacts the following respiratory parameters assessed daily from inclusion to weaning of deep sedation or 14 days after inclusion whichever comes first (PaO_2_/FiO_2_ ratio, pH, PaCO_2_, positive end-expiratory pressure (PEEP), VT, total PEEP, plateau pressure, driving pressure, respiratory rate, mechanical power (MP))To test whether ULTV is associated with an increase in sedation dose during the first 14 days after inclusionTo test whether ULTV is associated with an increase in rescue therapy during the first 14 days after inclusionTo test whether ULTV is associated with a decrease in the incidence density rate of adverse events during the first 28 days after inclusion (severe mixed acidosis, ventilator-associated pneumonia, acute cor pulmonale, barotrauma, any serious adverse events)To test whether ULTV is associated with cognitive impairment at day 365 after inclusionTo test whether ULTV is associated with quality-of-life impairment at day 365 after inclusionTo test whether ULTV is associated with post-traumatic stress disorder at day 365 after inclusionTo evaluate the efficiency of the innovative strategy performing a cost-effectiveness analysis at day 90 after inclusion

### Trial design {8}

The study is a multicenter prospective open-labeled, randomized controlled superiority trial, with two parallel groups and balanced randomization at a 1:1 ratio.

## Methods: participants, interventions, and outcomes

The third version of the protocol (Additional file 1) was published on April 12, 2020, before the inclusion of the 1st patient in the study. The current version is the fourth version of the protocol (Additional file 2), which was accepted on January 22, 2021, by the research ethics committee. Changes between versions 3 and 4 will be reported below. The WHO Trial Registration Data Set is provided in Additional file 3.

### Study setting {9}

The study will be conducted in 11 intensive care units located in both academic and non-academic French hospitals (Additional file 4).

### Eligibility criteria {10}

#### Inclusion criteria

Adults aged 18 years or olderARDS according to the Berlin Definition [9]COVID-19 pneumonia confirmed by a positive SARS-Cov-2 RT-PCR performed less than 7 days before inclusionInvasive mechanical ventilation with PaO_2_/FiO_2_ ≤ 150 mmHg and PEEP ≥ 5 cmH_2_O and with a VT ≤ 6 mL kg^−1^ PBW

#### Non-inclusion criteria

Exclusion criteria related to ARDS history
Onset of invasive or non-invasive ventilation more than 48 h before inclusionPrevious inclusion in the present studyExclusion criteria related to ARDS severity or complications
Arterial pH < 7.21 despite respiratory rate set to 35 min^−1^ at the time of inclusionPatient under any extracorporeal CO_2_ removal technique or extracorporeal membrane oxygenationPneumothorax or bronchopleural fistulaExclusion criteria related to comorbidities
Suspected intracranial hypertensionSevere chronic obstructive pulmonary disease defined by a GOLD score ≥ 3Chronic respiratory failure requiring long term oxygen or non-invasive ventilationObesity with body weight over height ratio greater than 1 kg cm^−1^Sickle cell diseaseBone marrow transplant < 6 months or neutropeniaBurn injury with extension greater than 30% of body surface areaCirrhosis with Child-Pugh score CAdvance directives to withhold or withdraw life-sustaining treatmentExclusion criteria related to legislation
Patient under an exclusion period relative to participation to another clinical trial, current inclusion into another clinical trial sharing the same primary endpoint as the present study, or inclusion into a clinical trial involving unlicensed new drugs or medical devices. Modification of this criterion was accepted by the research ethics committee on January 22, 2021, and co-inclusion into a clinical trial involving unlicensed new drugs or medical devices was no longer forbidden.Pregnancy.Patient under a legal protective measure.Lack of affiliation to social security as required by French regulation.Lack of written informed consent by the patient or next of kin.

### Who will take informed consent? {26a}

Before inclusion in the trial, written informed consent of patient’s the legal representative will be sought by local investigators, as all patients are expected to be unable to consent. If the patients’ legal representative could not be physically present for a written statement (e.g., transport restrictions relative to lockdown or quarantine), an emergency inclusion procedure could be used for inclusion, and study approval by the patients’ legal representative was later sought. In any case, patient’s written informed consent was sought as soon as its medical condition allowed this procedure.

### Additional consent provisions for collection and use of participant data and biological specimens {26b}

Potential future studies intending unplanned use of the data generated in this trial will require an additional consent of included patients. Unplanned use of biological specimens will not be performed.

### Interventions

#### Explanation for the choice of comparators {6b}

The control group will be managed with protective ventilation (i.e., VT 6 mL kg^−1^ PBW, PEEP set using the PEEP-FiO_2_ table of the low PEEP arm of the ALVEOLI trial [10], aiming for a plateau pressure < 30 cmH_2_O), as this strategy reflects a standard of care according to the national [11] and international guidelines [12].

#### Intervention description {11a}

Within the first hour after randomization, the control group will be managed with protective ventilation (i.e., VT 6 mL kg^−1^ PBW, PEEP set using the PEEP-FiO_2_ table of the low PEEP arm of the ALVEOLI trial [10], aiming for a plateau pressure < 30 cmH_2_O) under deep sedation (i.e., Richmond Agitation-Sedation Scale (RASS) score [13] between − 3 and − 4). Respiratory rate (RR) will be set targeting a pH range between 7.20 and 7.45, and VT may be increased if pH remains below 7.15 despite a RR set to 35 min^−1^ and minimization of instrumental dead space (Table 1).

**Table 1 Tab1:** Summary of the ventilation procedure

• Ventilatory mode: volume-assist control.	
• Instrumental dead space: minimize by using a heated humidifier and a low-volume endotracheal tube connector.	
• Control group: set VT to 6 mL kg^−1^ PBW.	
• Intervention group: stepwise reduction by 1 mL kg^−1^ PBW steps at intervals ≤ 2 h down to 4 mL kg^−1^ PBW and increase RR up to 35 min^−1^ to maintain VE constant.	
• Ratio of the duration of inspiration to the duration of expiration: adjust between 1:2 and 1:4 to maintain intrinsic PEEP ≤ 2 cm H_2_O.	
• Ventilatory goals: plateau pressure ≤ 30 cmH_2_O; 60 ≤ PaO_2_ ≤ 80 mmHg or 88% ≤ SpO_2_ ≤ 95%; 7.20 ≤ pH ≤ 7.45.	
• Allowable combinations of PEEP (cm of H_2_O) and FiO_2_: 5 and 30%, 5 and 40%, 8 and 40%, 8 and 50%, 10 and 50%, 10 and 60%, 10 and 70%, 12 and 70%, 14 and 70%, 14 and 80%, 14 and 90%, 16 and 90%, 18 and 90%, 20 and 100%, 22 and 100%, and 24 and 100%. Other combinations are allowed as a function of hemodynamic tolerance to PEEP.	
• Set ventilator alarms as follows: upper VT alarm set to 1.5 × set VT to identify double-triggering, upper RR alarm set to 37 min^−1^.	
• Procedure when PaO_2_ < 60 mmHg or SpO_2_ < 88% despite adjustments of FiO_2_ and PEEP (in the following order as needed): 1, use PP; 2, add NMBA; 3, add iNO; and 4, consider ECMO.	
• Procedure when PaO_2_ > 80 mmHg or SpO_2_ > 95% (in the following order as needed): 1, stop iNO; 2, stop NMBA if administration > 48 h; and 3, adjust FiO_2_ and PEEP.	
• Procedure when plateau pressure is > 30 cmH_2_O (in the following order as needed): 1, inject a bolus of NMBA; 2, reduce VT to 4 mL kg^−1^ PBW (if pH ≥ 7.20); and 3 decrease PEEP down to a minimum of 5 cmH_2_O.	
• Procedure when pH < 7.20 (in the following order as needed): 1, increase sedation/NMBA dose to achieve good patient-ventilator synchrony; 2, increase RR up to 35 min^−1^; 3, may administer IV bicarbonate; 4, increase VT by 1 mL kg^−1^ PBW step up to 8 mL kg^−1^ PBW if pH < 7.15; and 5, consider ECCOR or ECMO.	
• Procedure when pH > 7.45 (in the following order as needed): 1, decrease VT down to 4 mL kg^−1^ or 6 mL kg^−1^ PBW in the intervention and control groups, respectively, and 2, decrease RR	
• Procedure when VT > 4 mL kg^−1^ PBW and pH > 7.20 in the intervention group: attempt to decrease VT down to 4 mL kg^−1^ PBW at least twice daily.	
• Procedure when VT > 6 mL kg^−1^ PBW and pH > 7.20 in the control group: attempt to decrease VT down to 6 mL kg^−1^ PBW at least twice daily.	
• Procedure when RR > 35 min^−1^ or patient-ventilator asynchrony in patients treated with NMBA: inject a bolus of NMBA and increase maintenance dose.	
• Procedure when RR > 35 min^−1^ or occurrence of patient-ventilator asynchrony in patients without NMBA and either PaO_2_/FiO_2_ < 150 mmHg or PEEP > 8 cmH_2_O (in the following order as needed): 1, inject a bolus of sedation drugs and opioid and increase maintenance dose and 2, inject a bolus of NMBA and resume continuous NMBA administration.	
• Procedure when RR > 35 min^−1^ or patient-ventilator asynchrony in patients without NMBA and PaO_2_/FiO_2_ ≥ 150 mmHg and PEEP ≤ 8 cmH_2_O (in the following order as needed): 1, adjust I/E ratio; 2, inject a bolus of sedation drugs and opioid; 3, switch ventilatory mode to pressure support targeting VT between 6 and 8 mL kg^−1^; 4, inject a bolus of sedation drugs and opioid and resume deep sedation targeting RASS between − 3 and − 4 and decrease VT down to 4 mL kg^−1^ in the intervention group; and 5, bolus NMBA and resume continuous NMBA administration.	

*ECCOR* extracorporeal CO_2_ removal, *ECMO* extracorporeal membrane oxygenation, *FiO*_*2*_ fraction of inspired oxygen, *iNO* inhaled nitric oxide, *NMBA* neuromuscular blocking agent, *PaO*_*2*_ partial pressure of arterial oxygen, *PBW* predicted body weight, *PEEP* positive end-expiratory pressure, *PP* prone positioning, *RR* respiratory rate, *SpO*_*2*_ oxyhemoglobin saturation measured by pulse oximetry, *VE* minute-ventilation, *VT* tidal volume

Within the first hour after randomization, the intervention group will be managed with ultra-low tidal volume ventilation (i.e., aiming for VT 4 mL kg^−1^ PBW, PEEP set using the same PEEP-FiO_2_ table [10], aiming for a plateau pressure < 30 cmH_2_O) under deep sedation (i.e., RASS score between − 3 and − 4 [13]). RR will be set targeting a pH range between 7.20 and 7.45, and VT may be increased if pH remains below 7.15 despite a RR set to 35 min^−1^ and minimization of instrumental dead space (Table 1). This ventilatory protocol was successfully tested in a pilot randomized multicenter trial on 34 patients [8].

Adjustment of ventilatory settings in both groups will be predefined (Table 1). Both ventilatory strategies will be applied until the success of a deep sedation weaning trial (i.e., PEEP decrease down to 5 cmH_2_O with PaO_2_/FiO_2_ ≥ 150 mmHg in the supine position and VT 6 mL kg^−1^ PBW) performed daily from day 3 of the study. In case of ventilator asynchrony or RR > 35.min^−1^ despite ventilatory settings adjustments (Table 1), deep sedation will be resumed and ventilatory strategies will be reapplied according to the allocation group.

#### Criteria for discontinuing or modifying allocated interventions {11b}

Two situations are expected to require transient modification of allocated interventions, namely severe mixed acidosis and plateau pressure greater than 30 cmH_2_O.

Rules for handling severe mixed acidosis and excessive plateau pressure in the intervention group and the control group will be predefined (Table 1) and provided to the investigators in the full protocol document (Additional files 1 and 2) and in a summarized version (Additional file 5) allowing the availability of this information at the bedside.

After the resumption of severe mixed acidosis and excessive plateau pressure episodes, VT will be set according to the allocation group, and patients will be analyzed in their allocation group according to the randomization.

In case of harm related to the intervention, patients could be managed outside of the protocol at the attending physician’s discretion but will remain in their allocation group for data analysis. Patients could be withdrawn from the study at their request or at the request of their legal representative, and their data will not be analyzed.

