### Sample size {14}

The sample size was computed through data simulations based on the following hypotheses:
Ninety-day mortality 45% in the control group, and 40% in the intervention group (i.e., relative reduction 11%)Mean ± standard deviation (*SD*) VFD at day 60 28 ± 16.5 in the control group and 34.5 ± 13 in the intervention group

The expected mortality in patients with COVID-19 and moderate to severe ARDS is between 34 and 50% [1]. The mean and *SD* of VFD at day 60 in the control group was taken from the subgroup of patients with PaO_2_/FiO_2_ < 150 mmHg included in the control group of the prospective randomized Xtravent-study comparing ultra-protective ventilation with extracorporeal CO_2_ removal versus conventional protective ventilation [7]. To be conservative, we have chosen to take an expected difference between the two groups of the present study corresponding to 50% of the difference observed in the Xtravent-study between the control and the intervention groups.

For each scenario corresponding to a given sample size, 1000 datasets were simulated. For each simulation, the score was computed for each patient and compared between the two groups using the test of Mann and Whitney. The power was computed as the proportion of tests with a bilateral *p*-value < 0.05.

The results of the simulations allowed us to determine that the inclusion of 100 patients per group will achieve a power greater than 80% to conclude a significant difference between the groups.

The simulations were implemented by two biostatisticians with the SAS software, version 9.4 (Copyright (c) 2002–2003 by SAS Institute Inc., Cary, NC, USA) and the R software, version 3.6.1 (R Core Team (2012)). The results were similar.

To account for premature exits from the study (withdrawal of informed consent for example), we have planned to add 10% more patients (10 supplementary patients in each group for a total of 220 patients).

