#### Analysis of the primary outcome

The main analysis will be carried out by intention to treat, i.e., all the patients included in the study will be analyzed in their initial randomization group regardless of whether the allocated ventilation strategy was effectively applied or not.

The distribution of the composite score will be described in each group using the following statistics: mean, standard deviation, quartiles, and minimum and maximum values. It will be compared between the two groups using the test of Mann and Whitney.

The ULTV effect size will be quantified by the probability of a favorable result for a patient belonging to the ULTV arm in comparison with a patient belonging to the protective ventilation arm. This probability will be estimated by the proportion of pairs for which the patient of the ULTV arm will have a favorable result [20]. This estimate will be given with a 95% confidence interval.

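### Withdrawn patients are left out of the analysis although the main analysis is declared intention to treat on all included patients; the two rules conflict, and the exclusion can depend on outcome and arm

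*Protocol article*

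**What the plan says.** In the protocol article, section {11b} (criteria for discontinuing or modifying allocated interventions) allows withdrawal from the study by the patient's own choice or "at the request of their legal representative, and their data will not be analyzed". The sentence just before it treats another group differently: patients managed outside the protocol because of harm stay in their allocation group for analysis.

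Under *Analysis of the primary outcome*, the main analysis is by intention to treat: "all the patients included in the study will be analyzed in their initial randomization group regardless of whether the allocated ventilation strategy was effectively applied". The abstract also commits to intention-to-treat principles.

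Three other places bear on the point:

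- *Who will take informed consent? {26a}*: consent is sought from the legal representative, "as all patients are expected to be unable to consent". If the representative cannot attend, "an emergency inclusion procedure could be used for inclusion", with the representative's approval sought afterwards. In every case the "patient’s written informed consent was sought as soon as its medical condition allowed this procedure".
- *Sample size {14}*: "To account for premature exits from the study (withdrawal of informed consent for example), we have planned to add 10% more patients". This means 10 extra per group, 220 in total.
- Section {20c}: missing data are not imputed.

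**The concern.** A set that omits everyone who withdrew is not the set of all included patients. The qualifier in the intention-to-treat sentence concerns whether the allocated ventilation was applied; it makes no exception for withdrawal. Section {11b} itself separates off-protocol patients (kept) from withdrawn patients (not analysed), so the exclusion reads as a deliberate rule rather than loose wording.

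The exclusion is made after randomisation and can be related to outcome. A patient who dies before regaining capacity can never withdraw personally, so own-request withdrawals come from patients who recovered enough to decide. Withdrawals by a representative can occur while the patient is still critically ill and may include patients who later die. Section {17a} says that neither care providers nor outcome assessors are blinded, so a link between withdrawal and arm cannot be excluded.

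At stake are day-90 mortality and the primary composite, in which mortality ranks first. The planned mortality difference is only 5 points, so a few unevenly distributed exclusions are not negligible. The 10% over-recruitment restores numbers but not comparability between arms.

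**Working it through.** **Inputs from *Sample size {14}*.** Day-90 mortality 45% (control) and 40% (intervention); ventilator-free days 28 ± 16.5 and 34.5 ± 13; 100 per group plus 10 for exits.

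**Assumptions.** The number of withdrawals per arm, *w*, and the share of survivors among them, *s*, are not in the documents. The ventilator-free-day figures are taken to apply to survivors.

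**Plan's own figures.** 100 × 1.10 = 110 per arm, 220 in total, as stated. Simulating the score as written, compared by Mann-Whitney, gives 81% power at 100 per group, which agrees with the stated power above 80%.

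**Step 1: mortality within an arm.** With *D* expected deaths among 110, observed mortality is (*D* − *w*(1 − *s*)) / (110 − *w*). *D* is 49.5 in control and 44 in the intervention arm. At *w* = 10:

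| Survivor share among those excluded | Control | Intervention |
|---|---|---|
| 100% | 49.5/100 = 49.5% | 44/100 = 44.0% |
| 80% | 47.5/100 = 47.5% | 42/100 = 42.0% |
| same as in the arm (55%; 60%) | 45.0% | 40.0% |
| 0% | 39.5/100 = 39.5% | 34/100 = 34.0% |

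The sign of the bias turns at a survivor share of 55% in control and 60% in the intervention arm.

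**Step 2: comparison between arms, planned effect, survivors excluded.**

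| Excluded (control, intervention) | Control | Intervention | Difference (points) | Risk ratio |
|---|---|---|---|---|
| 0, 0 | 45.0% | 40.0% | −5.0 | 0.89 |
| 10, 10 | 49.5% | 44.0% | −5.5 | 0.89 |
| 2, 8 | 45.8% | 43.1% | −2.7 | 0.94 |
| 0, 10 | 45.0% | 44.0% | −1.0 | 0.98 |
| 10, 0 | 49.5% | 40.0% | −9.5 | 0.81 |

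**Step 3: composite.** Net benefit is the proportion of pairs won by the intervention patient minus the proportion lost. With mortality *m*C and *m*T, it equals (*m*C − *m*T) + (1 − *m*C)(1 − *m*T)·δ, where δ is the win-minus-loss proportion among pairs of survivors. With normal ventilator-free days, δ = 2Φ(6.5/√(16.5² + 13²)) − 1 = 2Φ(0.309) − 1 = 0.243.

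- Planned effect, nobody excluded: 0.05 + 0.55 × 0.60 × 0.243 = 0.130.
- 10 intervention survivors excluded: 0.01 + 0.55 × 0.56 × 0.243 = 0.085.
- 10 control survivors excluded: 0.095 + 0.505 × 0.60 × 0.243 = 0.169.
- 10 survivors excluded from each arm: 0.055 + 0.505 × 0.56 × 0.243 = 0.124.
- No true effect (45% in both arms, δ = 0), 10 versus 0 survivors: 0.495 − 0.45 = 0.045 in absolute value.
- No true effect, 5 versus 0: 49.5/105 − 0.45 = 0.021.

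**Step 4: false-positive rate.** Simulated with 110 per arm and no true effect, using a standard Mann-Whitney test on the hierarchical ranking at two-sided 0.05. Rejection is about 5% with no exclusion or 2 versus 0, about 6% with 5 versus 0, about 9% with 10 versus 0, and about 6% with 10 in each arm. These rates belong to that standard test. The cross-group score tested as written has a null rejection rate far from 5% for a separate reason, so it cannot serve as the baseline here.

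**The case against.** A reader might infer that withdrawn patients' data are deleted, that mostly survivors are lost, and that mortality is therefore biased upwards. The documents do not support this. Section {11b} says the data are not analysed; it does not mention erasure. It also gives the representative the right to withdraw, and under {26a} representatives are approached while the patient is incapacitated, so patients who later die can be withdrawn too. The first table in the working shows that the sign depends on the mix.

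Nor is higher mortality in both arms a biased treatment effect. Equal loss of survivors leaves the risk ratio at 0.89. No withdrawal rate by arm is given, so a difference between arms is a possibility and not a finding. The 10-versus-0 split is an extreme: it spends one arm's whole allowance, which covers all premature exits, on consent withdrawals by survivors only. Smaller imbalances have small effects on the false-positive rate.

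Finally, stopping the allocated ventilation already does not remove a patient, and the full protocol or an analysis plan, neither shown, may contain a withdrawal provision or a sensitivity analysis.

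All of this stands as a limit on direction and size. It does not remove the conflict: the article fixes both rules, they are incompatible, and nothing in it reconciles them. The point does not rest on missing detail.

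**Conclusion.** The point holds as a contradiction between two stated rules and as an avoidable risk of bias. It does not hold as a demonstrated bias in a known direction.

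The range is two-sided. With 10 of 110 control patients excluded, control mortality lies between 39.5% and 49.5% around a true 45%. If 10 survivors are lost from one arm only, the planned 5-point difference becomes 1.0 or 9.5 points, and net benefit moves from about 0.130 to 0.085 or 0.169. With no true effect, the false-positive rate is about 9% in that extreme case and about 6% with 5 versus 0. With balanced loss the comparison is almost unaffected.

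These figures rest on assumed numbers and survivor mix, since the documents supply only the allowance of 10 per arm. The change is worth making because it is cheap and the planned mortality difference is small.

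**What to change.** Reconcile section {11b} with the primary analysis section:

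- State that withdrawal from the study does not by itself remove a patient from the intention-to-treat analysis. Data collected up to withdrawal are kept, as are vital status and ventilation status afterwards where consent permits.
- Exclude only patients who refuse use of data already collected (directly or through their representative). Report their number by arm and by timing.
- If any such exclusions occur, call the analysed set modified intention to treat.
- Add one best-case/worst-case sensitivity analysis of the primary outcome for the excluded patients.

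The cost is one protocol sentence, matching wording in the information sheet, and one additional table. The sample size does not change.
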